## Abstract

Introduction

In the realm of dentistry, where precision and understanding of oral structures are paramount, the utilization of advanced technologies has revolutionized diagnostic and treatment methodologies. One such technology, palatography, holds significant importance in understanding the intricate dynamics of the oral cavity, particularly the interaction between the tongue and the palate during speech and swallowing. In the field of prosthodontics, achieving a successful outcome goes beyond simply restoring missing teeth. A well-designed denture or prosthesis should not only function properly but also consider factors like aesthetics, comfort, and speech intelligibility.

Methods

The speech quality analysis using artificial intelligence has been designed to assist in the palatal recontouring of complete dentures during the trial denture appointment and denture insertion. The study will be conducted on 12 completely edentulous patients, selected based on exclusion and inclusion criteria.

Expected results

The palatal recontouring assessment is expected to improve speech quality significantly. This could be incorporated into routine complete denture rehabilitation cases where the ease of technology can help enhance the phonetics of the prosthesis.

Conclusions

Patients undergoing full denture rehabilitation benefit greatly from phonetics. Taking this key factor into play through the use of advanced but readily available technology, palatography can be employed as a routine procedure for rehabilitation through complete dentures. There is definitely a learning curve involved while making it a routine procedure, but it is, nonetheless, a significant addition to holistic rehabilitation.

## Introduction

Speech is essential to human activity because it is a vital part of the stomatognathic system, which uses the oral cavity as a component of the voice. The vocal cords vibrate with the expiratory airflow allowing the larynx to create voice. Vowel formants are conditioned by the geometry of the resonance cavities, which in turn modulate the vocal cord tension, determining the laryngeal tone frequency. The tongue, gums, palate, alveolar processes, lips, and teeth are the speech articulatory organs [1,2]. Phonetics has to be seen alongside mechanics and aesthetics as the primary elements influencing dental prosthesis success [2,3].

It is important to make dentures that allow the patient to speak and voice themselves without any difficulties. Changes in the vertical dimension, size, and placement of the teeth, as well as the thickness and shape of the denture base, can all contribute to articulatory mistakes [1,2]. If other aspects of the maxillary full denture such as tooth location, occlusal vertical dimension, and occlusal plane are adequate, then accurately approximating the palatal contours with the patient's tongue can enhance speech intelligibility [4]. Maxillary dentures' artificial palatal vaults frequently have a concave contour. On the other hand, naturally occurring palatal vaults in the alveolar area have a convex form. Therefore, within a week following the placement of new dentures, the palatal vaults of maxillary dentures need to resemble natural ones in form to promote accurate pronunciation [5]. 

Research shows that many patients place a high value on speech sound production being undisturbed following dental treatment. The way that patients produce speech affects how satisfied they are with their dentures overall [6]. The aim of this study is to improve phonetics in a complete denture by functional palatal contouring during the try-in stage to improve the quality of life of patients.

## Materials and methods

Proposed study design

This experimental study will be conducted in the Department of Prosthodontics and Crown & Bridge, Sharad Pawar Dental College and Hospital, Wardha, Maharastra, India. The duration of the study will be six months. A total of 12 patients would be included in the study based on the inclusion and exclusion criteria (Table 1).

**Table 1 TAB1:** Inclusion and exclusion criteria

Inclusion Criteria	Exclusion Criteria
Patients indicated for a complete denture prosthesis.	Patient with macroglossia
Patients with Angles’s type 1 ridge relation.	Patients with congenital speech difficulty

Intended procedure

On the day of the trial denture appointment for the complete denture rehabilitation patient, the patient will be asked to read from a list of words. This will be recorded (Record A) through a microphone connected to artificial intelligence (AI) software, which will analyze the speech quality. After this, for palatography, food coloring will be applied to the palatal surface of the trial denture, and the patient will be asked to read from the previous list of words [7,8]. Based on the palatogram obtained using the food coloring, the palatal re-contouring would be done on the trial denture. Speech quality will be recorded again in the previously stated manner (Record B). After this, the denture fabrication will be done in a conventional manner. On the denture insertion appointment day, another recording (Record C) would be done wearing the complete denture in the same manner as previously stated. The values obtained from the AI software will be compared and analyzed statistically (Figure 1).

**Figure 1 FIG1:**
[figure not shown]
Flowchart of the study

Sample size

Mean difference formula was used to determine the sample size, n=[{(Z𝛼 + Z𝛽)2 𝛔2}/𝛿2], where Z𝛼 = 1.96 at 5% error and 95% confidence interval and Z𝛽 = 0.84 = Power at 99%. The primary variable is selected as Sh (Hz) linguopalatal contact and Wide Air Blade. Mean in Group 1 = 1170.6 ± 65.1. Mean in Group 2 = 1291.0 ± 67.8. Mean score difference (1291.0 - 1170.6) = 120.4. Pooled standard deviation = 66.45. Minimum sample size, n, = 12/record (group). As there will be three recordings, the total samples will be 12x3= 36.

Statistical analysis

An ANOVA test will be used to find the significant difference between the three groups for their mean evaluation of speech quality at the 5% level of significance.

Ethical considerations

The Datta Meghe Institute of Higher Education and Research's Institutional Ethics Committee has approved this study (approval number: DMIHER(DU)/IEC/2024/55) dated May 11, 2024. Research ethics rules shall be followed at all times, and participant anonymity will be protected.

Trial registration

The study was registered with the Clinical Trial Registry-India (CTRI) on July 9, 2024 (registration number: CTRI/2024/07/070341).

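### The sample size treats three recordings of the same 12 patients as independent groups, and the printed formula and inputs give 3, not the stated 12

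*Protocol article*

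**What the plan says.** The Protocol article, Materials and methods, Proposed study design, fixes enrolment: "A total of 12 patients would be included in the study". Under Intended procedure every patient gives three recordings. The first is made at the trial denture appointment: "This will be recorded (Record A) through a microphone connected to artificial intelligence (AI) software". Record B follows at that appointment, after the palate of the trial denture has been re-contoured. The third comes later: "On the denture insertion appointment day, another recording (Record C) would be done wearing the complete denture". All comparisons of A, B and C are therefore within patient.

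The Sample size paragraph begins: "Mean difference formula was used to determine the sample size". It prints n = (Zα + Zβ)²σ²/δ², with Zα = 1.96 and Zβ = 0.84, the latter labelled as 99% power. The planning values are a mean of 1170.6 (SD 65.1) in one group and 1291.0 (SD 67.8) in the other, a difference of 120.4, and "Pooled standard deviation = 66.45". The result is "Minimum sample size, n, = 12/record (group). As there will be three recordings, the total samples will be 12x3= 36".

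The Statistical analysis paragraph names an ANOVA at the 5% level and describes it as comparing three groups. The article gives neither an SD of within-patient differences nor a correlation between recordings.

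**The concern.** The design and the calculation do not match. When the same patients are measured repeatedly, the precision of a contrast depends on the SD of the differences within patients. The paragraph supplies only the SD of single measurements and calls each recording a group. The independent unit is the patient, of whom there are 12; the 36 are recordings.

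Two things follow. First, the stated calculation does not describe the power of the design being run, and its printed inputs do not lead to its printed answer. Second, a total of 36 samples, next to an ANOVA described as comparing three groups, could lead an analyst to run a one-way ANOVA with 36 − 3 = 33 error degrees of freedom. The within-patient analysis has (12 − 1) × (3 − 1) = 22. In a study of 12 patients, that choice could hide a moderate real improvement.

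**Working it through.** **Inputs, all from the Sample size paragraph:** δ = 1291.0 − 1170.6 = 120.4 Hz; σ = (65.1 + 67.8)/2 = 66.45 Hz; Zα = 1.96; Zβ = 0.84 as printed. The number of patients, 12, is from Proposed study design. The within-patient correlation ρ is **not** in the article; it is an assumption here, shown as a range.

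**Step 1: reproduce the stated 12.** σ²/δ² = 4415.60/14496.16 = 0.3046. Zβ is 0.84 for 80% power and 2.33 for 99%.

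| Formula | Zβ | n before rounding | n |
|---|---|---|---|
| As printed, (Zα + Zβ)²σ²/δ² | 0.84 | 2.80² × 0.3046 = 2.39 | 3 |
| As printed | 2.33 | 4.29² × 0.3046 = 5.61 | 6 |
| Two independent groups, 2(Zα + Zβ)²σ²/δ² | 0.84 | 4.78 | 5 |
| Two independent groups | 2.33 | 11.21 | **12** |

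Only the last row gives 12. The stated n therefore corresponds to independent groups at 99% power, not to the formula and Zβ on the page.

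**Step 2: power of 12 patients with a paired variance.** SD of differences = 66.45 × √(2(1 − ρ)). Power is for one paired contrast of 120.4 Hz, two-sided 5%, from the noncentral t with 11 degrees of freedom and noncentrality 120.4/(SD of differences/√12). The last column is the difference detectable with 80% power.

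| ρ (assumed) | SD of differences, Hz | Power for 120.4 Hz | Detectable at 80%, Hz |
|---|---|---|---|
| 0 | 94.0 | 98.1% | 83.6 |
| 0.3 | 78.6 | 99.8% | 69.9 |
| 0.5 | 66.5 | >99.9% | 59.1 |
| 0.7 | 51.5 | >99.9% | 45.8 |
| 0.8 | 42.0 | >99.9% | 37.4 |

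At ρ = 0.15 the power is already 99.2%. With the level divided by three for three pairwise contrasts, it is 92.5%, 98.5% and 99.9% at ρ = 0, 0.3 and 0.5. Only a negative correlation lowers it further (94.2% at ρ = −0.3, unadjusted).

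**Step 3: analysing 36 recordings as independent.** The variance of a contrast between two recordings is 2σ²(1 − ρ)/12. The independent-groups version is 2σ²/12, which is too large whenever ρ > 0. Simulation (100,000 trials, 12 patients × 3 recordings, equal correlation, nominal 5%) gives the following. The power columns take B and C both shifted by 0.6 SD, that is 0.6 × 66.45 ≈ 40 Hz, an illustrative value.

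| ρ (assumed) | Type I error, one-way | Power, one-way | Power, repeated-measures |
|---|---|---|---|
| 0 | 5% | 29% | 28% |
| 0.3 | 1.8% | 23% | 38% |
| 0.5 | 0.5% | 19% | 50% |
| 0.7 | 0.07% | 14% | 74% |

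The one-way test is conservative and loses power; it does not inflate false positives.

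**The case against.** The strongest reply is that little harm follows. The article states 12 patients in both the abstract and the methods, and the sentence giving 36 shows openly that it is 12 × 3 recordings. Nobody is told that 36 patients will be enrolled. With positive correlation the independent-groups calculation is conservative. Against the labelled 99%, the shortfall at ρ = 0 is 99 − 98.1 = 0.9 percentage points, and it is gone by ρ = 0.15. The exact form of the ANOVA may also be set out in an analysis plan that is not shown. All of this stands, and it limits the point to the stated calculation and its wording.

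Three stronger readings are tempting but not supported:

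- *That the planning SD comes from two separate sets of patients.* The article does not give the source of the two means and SDs, and it uses group as another word for record. The variance objection does not depend on the source: either way, no SD of differences is given.
- *That the plan overstates the precision of its comparisons.* Counting 36 units where there are 12 overstates the number of independent units. For contrasts between recordings with positive ρ, however, treating them as independent understates precision.
- *That the formula is a paired one that silently assumes ρ = 0.5.* The printed form, lacking the factor 2, would be a correct paired formula with this SD only at ρ = 0.5. But it did not produce the 12, so that assumption cannot be attributed to the plan.

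**Conclusion.** The point holds as a mismatch between calculation and design, together with an internal contradiction in the Sample size paragraph. The stated 12 matches an independent-groups calculation at 99% power (11.2 rounded up), whereas the printed formula and inputs give 2.4, so 3. Zβ = 0.84 belongs to 80% power and carries a 99% label.

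The point is not evidence that the trial is too small. If the planning difference and SD are accepted, 12 patients have at least 98.1% power for a single paired contrast at any ρ of zero or above. The risk lies in the analysis: if the 36 recordings are treated as independent, a difference of about 40 Hz would be detected with 19% rather than 50% power at ρ = 0.5. These figures rest on approximately normal values, equal correlation between recordings and assumed values of ρ. Whether a one-way analysis is intended cannot be settled from the article; its wording leaves that open.

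**What to change.** 1. Restate the total as: *12 patients, each recorded three times (36 recordings); the unit of analysis is the patient.*
2. Replace the calculation with a paired one: give the SD of differences over a stated range of ρ, with the power for 120.4 Hz and the difference detectable with 12 patients. The second table under the working can serve as a template.
3. Reconcile Zβ = 0.84 with the 99% power label, and the printed formula with n = 12.
4. Make the Statistical analysis sentence match by naming a repeated-measures (within-patient) ANOVA.

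The cost is rewording one paragraph and one sentence. Enrolment, procedures and data collection do not change.

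### Three recordings of the same 12 patients are to be compared by an ANOVA worded as between groups, with no patient term; run as an ordinary one-way ANOVA, it would give standard errors that are too wide

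*Protocol article*

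**What the plan says.** The Proposed study design section of the Protocol article enrols one cohort: "A total of 12 patients would be included in the study". Under Intended procedure, Record A is made with the trial denture before recontouring. After recontouring, "Speech quality will be recorded again in the previously stated manner (Record B"). At denture insertion, "another recording (Record C) would be done wearing the complete denture in the same manner as previously stated". Every patient therefore supplies all three records.

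The Sample size section equates record with group, sets 12 per record, and adds: "As there will be three recordings, the total samples will be 12x3= 36".

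The Statistical analysis section consists of one sentence: "An ANOVA test will be used to find the significant difference between the three groups for their mean evaluation of speech quality", to be tested "at the 5% level of significance". It does not mention repeated measures, pairing or a patient effect, and it does not say whether the ANOVA is one-way.

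**The concern.** The research question is within-patient: does recontouring change the same person's speech? Three values from one speaker share that speaker's voice and are very likely to be positively correlated. A one-way ANOVA on 36 values leaves the differences between patients in the error term and assumes independence, which this design does not have.

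At stake are the standard errors, confidence intervals and p-values of the only hypothesis test that the article states. With 12 patients, using each as their own control is the main source of precision, and a one-way analysis gives it up.

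**Working it through.** **Inputs.** From the Sample size section: means 1170.6 and 1291.0 Hz, difference 120.4 Hz, SD 66.45 Hz, 12 per record, "1.96 at 5% error and 95% confidence interval", and "0.84 = Power at 99"%. From the Statistical analysis section: a 5% level. The within-patient correlation ρ is not given. It is assumed here to be 0, 0.3, 0.5 or 0.7.

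**Step 1. Reproduce n = 12, to see which design the planning assumes.**
- Printed formula with 0.84: (1.96 + 0.84)² × 66.45² / 120.4² = 2.39, so 3.
- Same formula with the normal quantile for 99% power (2.326): 5.60, so 6.
- Independent two-sample formula at 80% power: 2 × (1.96 + 0.84)² × 66.45² / 120.4² = 4.78, so 5.
- Independent two-sample formula at 99% power: 2 × (1.96 + 2.326)² × 66.45² / 120.4² = 11.19, so **12**.

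Of these, only the last gives the stated figure. It uses a pooled two-group SD, not an SD of within-patient differences, so the planning treats the records as independent groups. (The mismatch between 0.84 and 99% power is a separate matter.)

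**Step 2. Standard error of a difference between two records**, assuming equal variances and equal correlations.
- As a one-way ANOVA would report it: σ√(2/12) = 66.45 × 0.408 = 27.1 Hz, whatever ρ is.
- True value: σ√(2(1−ρ)/12).
- Ratio: 1/√(1−ρ).

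| ρ | True SE (Hz) | One-way SE (Hz) | Ratio |
|---|---|---|---|
| 0 | 27.1 | 27.1 | 1.00 |
| 0.3 | 22.7 | 27.1 | 1.20 |
| 0.5 | 19.2 | 27.1 | 1.41 |
| 0.7 | 14.9 | 27.1 | 1.83 |

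**Step 3. Type I error and power by simulation.** Normal data, 12 patients × 3 records, SD 66.45, compound symmetry, at least 100,000 runs per setting. The one-way test is F(2, 33) and the repeated-measures test is F(2, 22). The power columns take A as differing from B = C. Each cell is one-way vs repeated-measures.

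| ρ | Type I error | Power, 120.4 Hz | Power, 60.2 Hz | Power, 40.1 Hz |
|---|---|---|---|---|
| 0 | 5% vs 5% | 99.5% vs 99.3% | 58% vs 56% | 29% vs 28% |
| 0.3 | 1.7% vs 5% | 99.8% vs >99.9% | 57% vs 72–73% | 23% vs 38% |
| 0.5 | 0.5% vs 5% | 99.9% vs >99.9% | 57% vs 87% | 19% vs 51% |
| 0.7 | 0.1% vs 5% | >99.9% vs 100% | 56% vs 98% | 15% vs 74% |

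The effects of 60.2 and 40.1 Hz are one half and one third of the planning difference. They were chosen for illustration and do not come from the document. With a graded pattern (0, 60.2, 120.4 Hz) both tests have about 97% power at ρ = 0, and at ρ = 0.3 to 0.7 the one-way test has about 99% or more.

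**The case against.** The strongest reply is that the article never says one-way or independent. A repeated-measures ANOVA is an ANOVA, and a condensed article may leave the exact model to a fuller document. The article also uses the word groups for conditions within patients: its Discussion describes a cited study of three patients, each recorded under several denture conditions, as having five speech groups. The total of 36 is a correct count of recordings. The printed sample-size formula, lacking the factor 2, even has the one-sample or paired form.

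Much of this stands. A reader might infer that the plan states an independent-groups analysis; it does not, and that reading is an inference. Three things still support it: the comparison is worded as between groups, no patient term is given, and n = 12 needs the two-sample formula. The Discussion also reports a cited study of 10 patients recorded under four denture conditions and analysed by a paired t test, so pairing is not foreign to the article. The test and the comparison are stated here, not deferred, and the wording does not fit the design.

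A second reply is that the consequence is mild. The error is conservative, so a significant result would not be a false claim on this account. The larger power losses need both a true effect well below plan and a moderate or high ρ. That is right, and it limits the point.

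**Conclusion.** The point holds in a limited form. The stated test does not match a design in which the same 12 patients supply all three records, and following the text most naturally leads to a one-way ANOVA. Its standard errors would then be too wide for any positive within-patient correlation, by 1.2 to 1.8 times for ρ from 0.3 to 0.7, and its true type I error would fall to between 1.7% and 0.1%. At ρ = 0 neither problem arises.

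A reader might go further and infer that the trial as planned suffers a large loss of power. The document's own figures do not support that: at 120.4 Hz and SD 66.45 the one-way test already has over 99% power when A differs from B = C. The loss is conditional on a smaller true effect and on a ρ that the document does not give. Nor is there any inflation of false positives when ρ is positive.

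The figures rest on assumed ρ, equal variances and correlations, normal data and the planning SD.

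**What to change.** Replace the sentence under Statistical analysis with: *Records A, B and C will be compared by repeated-measures ANOVA with patient as the within-subject blocking factor (Greenhouse-Geisser corrected) at the 5% level, followed by paired within-patient differences with 95% confidence intervals.*

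The cost is one sentence. Patients, visits and recordings stay the same. The error degrees of freedom fall from 33 to 22, which costs a little power only if ρ is near zero (at 60.2 Hz, 58% to 56%).

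### The aim concerns the finished complete denture, but the one stated test is an omnibus ANOVA that is equally likely to be significant whether or not that denture is better

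*Protocol article*

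**What the plan says.** The Introduction of the protocol article gives the aim: "The aim of this study is to improve phonetics in a complete denture by functional palatal contouring during the try-in stage". The Results section adds a scope of making functional contouring a standard step in complete denture fabrication.

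Under Materials and methods, Intended procedure, three recordings are made:

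- Record A: trial denture before recontouring, "This will be recorded (Record A) through a microphone connected to artificial intelligence (AI) software".
- Record B: the same trial denture after recontouring.
- Record C: finished denture at the insertion appointment, "another recording (Record C) would be done wearing the complete denture in the same manner as previously stated".

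Between B and C comes the processing step: "After this, the denture fabrication will be done in a conventional manner".

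The Statistical analysis section is one sentence. It plans an ANOVA, with significance set at 5%, whose purpose is to "find the significant difference between the three groups for their mean evaluation of speech quality". Intended procedure says only that the software's values will be compared and analysed statistically. No pairwise comparison, contrast or direction is given. Sample size works with a mean difference of 120.4, a pooled SD of 66.45 and 12 per record. The same 12 patients give all three records.

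**The concern.** The intervention is carried out on the trial denture, but the aim is about the complete denture. Record C is the only recording of that denture, so the comparison that bears on the aim is C against A.

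An omnibus ANOVA asks only whether the three means differ somewhere. A real B-A difference is enough to make it significant, wherever C lies. C could be as good as B, no better than A, or worse than A. The stated criterion would be met in all three cases, and it carries no information on which one occurred. At stake is whether the trial's only stated test can support a sentence about the denture that the patient takes home.

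**Working it through.** **Inputs.** From Sample size: difference d = 120.4 (Sh, in Hz), SD = 66.45, n = 12 per record. From Statistical analysis: alpha 0.05. Assumptions made here: d is taken as the try-in gain, SDs are equal, and within-patient correlations (not given in the article) are varied.

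**Reproducing the plan's figure.** The two-sample formula at 99% power gives n = 2 × (1.96 + 2.326)² × 66.45² / 120.4² = 11.19, so 12, which matches. The formula as printed, with 0.84 and no factor 2, gives 2.39. That mismatch is a separate matter. What counts here is that 12 comes from comparing two means, and that d, SD and n are the plan's own.

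**Omnibus test, gain kept against gain lost.** The noncentrality is λ = n × Σ(mean − grand mean)² / SD².

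- Gain fully kept, (A, B, C) = (0, d, d): deviations −2d/3, d/3, d/3. Sum of squares (4 + 1 + 1)d²/9 = (2/3)d² = 9664.1.
- Gain fully lost, (0, d, 0): deviations −d/3, 2d/3, −d/3. Sum of squares (1 + 4 + 1)d²/9 = (2/3)d² = 9664.1.
- Both give λ = 12 × 9664.1 / 66.45² = 26.26.
- C worse than A by d, (0, d, −d): sum of squares 2d² = 28992.3, λ = 78.79.

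One-way ANOVA (2 and 33 degrees of freedom):

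| True pattern in C | λ | Probability of p < 0.05 |
|---|---|---|
| Gain fully kept | 26.26 | 99.5% |
| Half the gain kept, (0, d, d/2) | 19.70 | 97.4% |
| Gain fully lost | 26.26 | 99.5% |
| C below A by d | 78.79 | above 99.9% |

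The equality of kept and lost is algebraic and holds for any d. At d/2 both give 58.3%, and at d/4 both give 17.8%.

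**Does it matter which ANOVA is meant?** No. For repeated measures (2 and 22 degrees of freedom), λ becomes 26.26/(1 − ρ) with a common correlation ρ. Power is then 99.3% (ρ = 0), 99.96% (0.3) and above 99.99% (0.5 or more), identical for kept and lost. With unequal correlations (0.8 for A-B, 0.4 for A-C and B-C), simulation of 20,000 trials per case gives nearly equal rates for kept and lost: 100% and 100% at d, 92.4% and 92.7% at d/2, 46.6% and 45.5% at 0.3d.

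**A test that separates the cases.** Paired t-test of C-A, 11 degrees of freedom, SD of the change = 66.45 × √(2(1 − ρ)):

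- Gain kept: power 98.1% (ρ = 0), 99.8% (0.3), above 99.9% (0.5 or more).
- Gain lost: rejection at the 5% level by construction (simulated 5.3% at ρ = 0 and 4.9% at ρ = 0.5).

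**Precision of a paired change.** The 95% CI half-width is 2.201 × 66.45 × √(2(1 − ρ)) / √12, which is 50, 42, 33 or 19 Hz at ρ = 0.3, 0.5, 0.7 or 0.9.

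**The case against.** The strongest reply is that this is a condensed article. Follow-up comparisons after a three-level ANOVA are commonly left to the full protocol or analysis plan, and every three-group omnibus test has the property shown. That stands as far as it goes: the absence of post hoc tests is not the point. The point is that the article does fix a test and a level, and that the test does not correspond to the stated aim.

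Second, a reader might infer that a significant ANOVA would be reported as benefit in the finished denture even if processing removed the whole gain. The document does not say so. The three observed means would be visible, and a C mean back at the level of A would be noticed. What remains is that no stated inference is attached to those means.

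Third, a reader might infer that the trial must prove the try-in gain is retained, or that a non-significant B-C difference would be taken as retention. Neither is in the document. The aim is met by a finished denture that is better than baseline, even if somewhat below Record B, so a retention margin would go beyond it.

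Fourth, C-A is not a clean measure of recontouring. It compares an unmodified trial denture with a finished denture at a later appointment. This stands and limits what the fix can deliver.

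**Conclusion.** The concern holds in a limited form. The one stated test does not answer the aim for the finished denture. Its probability of significance is 99.5% when the gain is fully kept and 99.5% when it is fully lost, and it also rejects when C is worse than A. A significant result alone therefore does not show that the finished denture is better.

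The equality is one of rejection probability, not of the F value in a given data set. It is exact with equal SDs and equal correlations, and close to exact in the unequal-correlation case tried. The 99.5% rests on the article's 120.4 and 66.45. The correlations are assumptions, but the conclusion does not depend on them. The document does not support the stronger statement that the trial will reach a wrong conclusion.

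**What to change.** In Statistical analysis:

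1. Name the within-patient change C-A, with its 95% CI and a paired test at the 5% level, as the comparison that answers the aim for the finished denture. State which direction counts as improvement on the chosen measure.
2. Report B-A and C-B with 95% CIs as supporting results. No retention margin is needed.
3. If C-A does not show improvement, limit the conclusion to the trial denture.
4. State that C-A also includes the change from trial to finished denture and the later visit, so it does not by itself attribute the change to recontouring.

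The ANOVA can stay as an overall summary. The cost is a few lines of text and slightly more analysis of recordings already planned in the same 12 patients. The trade-off is a stricter basis for claiming benefit in the finished denture.

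### The one stated test compares all three records at once, so a significant result would not show that recontouring changed speech; the paired B − A difference should be the primary comparison

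*Protocol article*

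**What the plan says.** The aim, at the end of the Introduction, is better phonetics in a complete denture through "functional palatal contouring during the try-in stage to improve the quality of life of patients".

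Under Intended procedure (Materials and methods), each patient gives three recordings:

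- **Record A:** trial denture, before recontouring.
- **Record B:** the same trial denture at the same appointment, after recontouring. Between A and B the word list is read once more to obtain the palatogram.
- **Record C:** the finished denture, made conventionally after the try-in: "On the denture insertion appointment day, another recording (Record C) would be done wearing the complete denture in the same manner as previously stated".

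The Statistical analysis paragraph is one sentence: an ANOVA is to look for a "significant difference between the three groups for their mean evaluation of speech quality at the 5% level of significance". It names no contrast and does not say whether the ANOVA is for repeated measures or independent groups. The Sample size paragraph rests on a difference between two means ("Mean score difference (1291.0 - 1170.6) = 120.4", "Pooled standard deviation = 66.45"), and those two means are not tied to A, B or C.

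**The concern.** The question is whether recontouring at try-in changes speech. The comparison closest to it is A with B, where the denture and the visit stay the same and the palatal contour is changed. Record C differs from both in two further ways: it is taken with a different, processed denture and on a later day. No finished denture without recontouring is recorded, so nothing separates these influences within C. The Introduction itself lists thickness and shape of the denture base among the causes of articulatory error, so a shift in C for other reasons is plausible.

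A one-factor ANOVA over three levels asks only whether any of the means differ. It says neither which records differ nor in which direction. The Abstract expects recontouring to improve speech quality significantly, and a significant F could be taken as confirming that even if A and B were alike.

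**Working it through.** **1. The plan's own figure.** Inputs from Sample size: difference 120.4, SD 66.45, "1.96 at 5% error and 95% confidence interval", and "0.84 = Power at 99"%. The ratio 66.45²/120.4² is 4415.6/14496.2 = 0.3046.

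- Two-sample formula at 99% power (z = 2.326): 2 × (1.96 + 2.326)² × 0.3046 = 11.19, rounded up to 12. This reproduces the stated number.
- Formula and z as printed: (1.96 + 0.84)² × 0.3046 = 2.39, rounded up to 3. This does not.

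So the 12 comes from a comparison of two means. The mismatch between z = 0.84 and 99% power is a separate matter.

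**2. What the F test does when recontouring has no effect.** Set A = B and shift C alone by d SD, with n = 12. Neither d nor the within-patient correlation ρ is in the article; both are assumed and shown as a range, with equal correlation between all pairs of records.

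For the repeated-measures F test (2 and 22 degrees of freedom), the means (0, 0, d) have a sum of squares about their average of (2/3)d². The noncentrality is therefore 12 × (2/3)d²/(1 − ρ) = 8d²/(1 − ρ). For example, d = 0.5 and ρ = 0.5 give 8 × 0.25/0.5 = 4.0, and a rejection probability of 37%. Rejection rates for the independent-groups F test (2 and 33 degrees of freedom) and the paired test are simulated.

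| Test | ρ | d = 0.2 | d = 0.5 | d = 0.8 | d = 1.0 |
|---|---|---|---|---|---|
| Repeated-measures F | 0 | 7% | 20% | 46% | 65% |
| Repeated-measures F | 0.5 | 9% | 37% | 77% | 93% |
| Repeated-measures F | 0.8 | 17% | 76% | 99% | 100% |
| Independent-groups F | 0 | 7% | 21% | 48% | 68% |
| Independent-groups F | 0.5 | 1% | 11% | 42% | 69% |
| Independent-groups F | 0.8 | 0% | 5% | 38% | 71% |
| Paired A versus B | all three | about 5% | about 5% | about 5% | about 5% |

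On the plan's own scale, a C shift of 60.2 Hz (half of 120.4, or 0.91 SD) gives 57% at ρ = 0 and 86% at ρ = 0.5 for repeated measures, and 56–59% for independent groups.

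**3. Does the paired comparison work with 12 patients?** The SD of the within-patient difference is 66.45 × √(2(1 − ρ)), and the noncentrality is 120.4 × √12 divided by that SD.

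- ρ = 0: SD 93.97, noncentrality 4.44, power 98.1%.
- ρ = 0.3: SD 78.62, noncentrality 5.30, power 99.8%.
- ρ = 0.5: SD 66.45, noncentrality 6.28, power above 99.9%.

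These use two-sided 5% and a t distribution with 11 degrees of freedom. No further patients are needed.

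**The case against.** **Pairwise tests may be planned elsewhere.** A condensed article often leaves comparisons after an ANOVA to the analysis plan, which is not shown. This stands in part: it is only of this article that one can say the omnibus test is the sole stated one. But the article does not leave the test open. It fixes an omnibus ANOVA, and post hoc tests added later would not make A versus B the primary comparison.

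**The percentages are not false-positive rates.** This stands in full. A reader might set them against the 5% level and infer an inflated type I error. In every shifted scenario A = B = C is false, so rejection is correct. With all three means equal, the repeated-measures F test rejects about 5% of the time, and the independent-groups version about 0.5% at ρ = 0.5. The risk lies in what the rejection is attributed to.

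**A versus B is not clean either.** This also stands. Order is fixed, there is no control, and the list is read again for the palatogram, so B is at least the third reading. B − A is the best available contrast, but it includes practice.

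**The finished denture is part of the question.** The aim names the complete denture, and the Abstract covers both the try-in and insertion appointments. One might infer that A versus C should be merely descriptive; the article does not require that. It is a legitimate secondary comparison.

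**Sizing on two means does little harm.** At 120.4 and 66.45 with 12 per record, an independent three-group F test has about 97% power in the least favourable pattern of means. This stands: the two-mean basis shows which analysis fits the calculation, not a shortage of patients.

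**Conclusion.** The point holds as a mismatch between the stated test and the stated aim. A significant three-record ANOVA would not establish that recontouring changed speech, because C alone can produce it. How often depends on two quantities that the article does not give. For C shifts of 0.2 to 1.0 SD and correlations of 0 to 0.8, rejection with A = B runs from 7% to about 100% for a repeated-measures F test, and from about 0% to 71% for an independent-groups one. At small shifts the problem is slight. Nor does the text say which version is meant, so neither row of figures can be called the planned test.

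This should be fixed before the analysis. It does not invalidate the design: the records needed for the better comparison are already part of the procedure, and 12 patients give it about 98% power or more at the plan's own difference and SD.

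**What to change.** Replace the Statistical analysis sentence with text to this effect:

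- **Primary:** the paired within-patient difference B − A, two-sided 5%, with its 95% confidence interval.
- **Secondary:** A versus C and B versus C, as questions about the finished denture, with control for multiplicity (for example Holm).
- **Supportive:** a repeated-measures test across the three records.
- **Interpretation:** B − A best isolates recontouring but still includes practice, because the order is fixed, there is no control and the list is read again between the two recordings. Differences involving C also carry the change of denture and of visit.

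The Sample size paragraph should say that its two means stand for the B − A comparison. The cost is analysis wording only, with no new patients or recordings. The change should be made before the data are analysed, which the Results section places in early 2025.
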